### Study Outcomes

We defined the primary outcome as a change in albuminuria levels in the first-morning void over 12 months. A first-morning void is less influenced by hydration and physical activity than a spot urine sample [22-25]. As the participants in this study are restricted to patients with microalbuminuria but without macroalbuminuria, we validated albuminuria in a first-morning void.

The secondary outcomes were changes in physical parameters (BMI and BP), blood tests, lifestyle habits, self-management, medication therapy, adherence to the diabetes medication regimen, and quality of life (QoL). Blood test parameters included renal function (eGFR), glycemic control (HbA_1c_ and fasting blood glucose), and lipid metabolism (high-density lipoprotein cholesterol [HDL-C], low-density lipoprotein cholesterol [LDL], and triglycerides [TG]). We also assessed all-cause deaths, composite cardiovascular outcomes, composite renal endpoints, safety, and the usage frequency of DialBetesPlus.

Changes in lifestyle habits were assessed via food-log diaries covering 3 days. Dietitians calculated caloric intake and nutrient balance. The Summary of Diabetes Self-Care Activities Measure (SDSCA)—which evaluates 7 aspects of the diabetes regimen: general diet, specific diet, exercise, medication taking, blood-glucose testing, foot care, and smoking—is a widely used self-reporting tool for patients with diabetes in the United States [26]. We evaluated changes in self-management using the Japanese version of the SDSCA, the J-SDSCA. Change in medication therapy was assessed by evaluating prescriptions. Diabetes medication adherence was monitored using the 8-item Morisky Adherence Scale (MMAS-8). The MMAS-8 is reliable and valid in measuring the adherence of patients with multiple chronic conditions worldwide, including T2DM [27-29]. We measured patients’ QoL using the Japanese version of the Audit of Diabetes-Dependent Quality of Life (JP-ADDQoL). The ADDQoL is a diabetes-specific QoL measurement scale producing reliable and valid scores [30,31]. JP-ADDQoL also showed adequate reliability and acceptable validity [32].

Composite cardiovascular outcomes included the first occurrence and recurrence of myocardial infarction and stroke, the first occurrence of percutaneous coronary intervention and coronary artery bypass, hospitalization for unstable angina and heart failure, and cardiovascular death. The composite renal endpoint was defined as ESRD and more than a 2-fold increase in serum creatinine.

To ensure safety, we monitored the number of hypoglycemic events, other adverse events, and issues with the DialBetesPlus system throughout the study. The results of the hospital-led model and the pharmacy-led model will also be compared.

### Data Collection

At registration, we collected information on patients’ background, albuminuria level in a first-morning void, physical parameters, medications, blood tests, food-log diaries, J-SDSCA, MMAS-8, and JP-ADDQoL. Follow-up visits were scheduled at 2 months (plus or minus 4 weeks), 6 months (plus or minus 6 weeks), 12 months (plus or minus 6 weeks), and 18 months (plus or minus 6 weeks). We collected and recorded information according to the schedule in Table 1. Even if the interventional treatment was discontinued, we collected as much information as possible with the consent of participants.

**Table 1 table1:** Assessment and follow-up schedule.

Assessments	Follow-up period				
	Registration	2 months	6 months	12 months	18 months
Patient background	●				
Albuminuria level in a first-morning void	●			●	●
Albuminuria level in a spot urine			●		
Physical parameters	●		●	●	●
Medication therapy	●	●	●	●	●
Blood test	●	●	●	●	●
Dietary intake log	●		●	●	●
J-SDSCA^a^	●		●	●	●
MMAS-8^b^	●			●	●
JP-ADDQoL^c^	●			●	
All-cause death		●	●	●	●
Composite cardiovascular outcome		●	●	●	●
Composite renal endpoint		●	●	●	●
DialBetesPlus safety questionnaire				●	
Safety		●	●	●	●
DialBetesPlus usage frequency			●	●	

^a^J-SDSCA: Japanese version of the Summary of Diabetes Self-Care Activities Measure.

^b^MMAS-8: 8-item Morisky Adherence Scale.

^c^JP-ADDQoL: Japanese version of the Audit of Diabetes-Dependent Quality of Life.

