### Participants

We recruited patients who passed all the inclusion and exclusion criteria before randomization (Textbox 2). The criteria were designed to include T2DM patients experiencing the early stage of DKD without any restrictions on physical activity. Eligible participants had T2DM with microalbuminuria (30-299 mg/g creatinine), hemoglobin A_1c_ (HbA_1c_) of 6.5% or more, and an estimated glomerular filtration rate (eGFR) of 45mL/min/1.73m^2^ or more. We obtained written, informed consent from all the patients participating in this study. Prior to the randomization, all enrolled patients were asked to use DialBetesPlus for 2 weeks to confirm their ability to use the system and devices properly. Eligible participants were those able to use DialBetesPlus for over 7 days during the initial 2-week confirmation period. The participants were randomized into either the intervention or control group in a one-to-one fashion based on albuminuria levels, gender, and age. The research team consisted of diabetologists, nephrologists, pharmacists, dieticians, nurses, a laboratory technician, and technical support experts. While the team handled technical troubles and monitored usage of the system, the patients continued to consult their attending doctors about their general health status. If 7 days passed without any input into the system, an alert was sent to encourage the patient to resume providing input. If 3 weeks passed without a patient inputting any data, we defined the patient as a dropout. Participants with whom the study team has lost contact were also treated as dropouts. The criteria for study discontinuance were a serious adverse event, patient request for discontinuance, pregnancy, or the judgment of a lead physician.

Inclusion and exclusion criteria.

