### Sample Size

The primary outcome of this study is a change in albuminuria levels at 12 months. We estimated that baseline first-morning-void albuminuria level would be 200 plus or minus 200 mg/g creatinine and hypothesized the difference in the change in albuminuria between the intervention group and the control group at 12 months would be 100 plus or minus 200 mg/g creatinine. Based on previous reports [20,21], we calculated 63 patients were required in each group to achieve a 2-sided significance level of .05 and a statistical power of 80%. Factoring ineligibility and dropouts, we calculated a final target number of 80 patients per group.

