**Laboratory test, median (Q1-Q3)**										
	Fasting plasma glucose (mg/dL)	144.0 (124.0-174.0)		139.0 (124.0-159.0)		150.0 (123.0-185.0)		.37		
	HbA_1c_^b^ (%)	7.5 (7.0-8.0)		7.4 (6.9-7.9)		7.5 (7.1-8.1)		.31		
	LDL^c^ cholesterol (mg/dL)	99.0 (78.0-117.0)		106.0 (78.0-117.0)		98.0 (83.0-112.0)		.55		
	HDL^d^ cholesterol (mg/dL)	49.5 (42.9-60.8)		49.0 (44.0-60.8)		50.0 (42.0-60.5)		.64		
	Triglycerides (mg/dl)	155.5 (100.0-261.0)		149.0 (100.0-261.0)		158.0 (100.0-252.0)		.64		
	Creatinine (mg/dL)	0.78 (0.65-0.92)		0.82 (0.68-0.93)		0.78 (0.62-0.92)		.33		
	eGFR^e^ (mL/min/1.73m^2^)	72.0 (61.8-85.3)		71.0 (63.8-83.0)		76.5 (59.5-85.5)		.29		
	UACR^f^ (mg/gCr)	36.4 (15.1-76.2)^g^		32.3 (14.8-70.6)		41.0 (15.1-78.0)		.49		

^a^BP: blood pressure.

^b^HbA_1c_: glycated hemoglobin.

^c^LDL-C: low-density lipoprotein cholesterol.

^d^HDL-C: high-density lipoprotein cholesterol.

^e^eGFR: estimated glomerular filtration rate.

^f^UACR: urine albumin-to-creatinine ratio.

^g^One case had a missing value.

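### As worded, the primary outcome rests on one first-morning void at each end, so within-person albuminuria noise enters the change score twice; this is an inefficiency, not a sample size error

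*Protocol article*

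**What the plan says.** Study Outcomes states: "We defined the primary outcome as a change in albuminuria levels in the first-morning void over 12 months". Data Collection names, among the registration measurements, "albuminuria level in a first-morning void, physical parameters, medications, blood tests". Table 1 carries one mark for the first-morning void at registration, one at 12 months and one at 18 months, with a spot urine at 6 months. The COVID-19 section also speaks of a single mailed void. Nowhere does the article mention repeat voids or averaging.

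For eligibility, Textbox 2 asks for two spot urine results in the microalbuminuria range (30-299 mg/g creatinine). Statistical Analysis compares changes between groups by t test or Mann-Whitney test and names no baseline adjustment.

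Sample Size assumes that "baseline first-morning-void albuminuria level would be 200 plus or minus 200 mg/g creatinine", and that the difference in change between "the intervention group and the control group at 12 months would be 100 plus or minus 200 mg/g creatinine". From this, "we calculated 63 patients were required in each group to achieve a 2-sided significance level of .05 and a statistical power of 80" per cent. Table 2 reports 61 control and 69 intervention patients, with a baseline median of 36.4 mg/g and quartiles of 15.1 and 76.2.

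**The concern.** Albuminuria varies from day to day within a patient. When the outcome is one reading minus another, the variance of the change is the variance of the true change plus twice the within-person variance of a single reading. Adjusting for baseline can offset part of the noise in the first reading. No analysis of a single pair can remove the noise in the second.

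The plan itself treats urine variability as a concern. It prefers the first-morning void because that specimen is less sensitive to fluid intake and exertion, and it does not accept a single result for eligibility. Yet the endpoint that decides the trial uses one reading at each end. With about 130 patients, a real effect of moderate size could be missed partly because of sampling noise.

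**Working it through.** **1. The plan's own figure.** Inputs from Sample Size: difference 100, SD 200, two-sided 0.05, power 80%, 1:1 allocation.

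n per group = 2 × (1.96 + 0.8416)² × 200² / 100² = 62.8, so 63. The stated figure reproduces, with power 80.1% at 63. The SD of 200 is attached to the change. If it came from single-void data, the noise is already in it.

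**2. Variance of the change with k voids at each end.** Let s_c be the SD of true 12-month change, s_w the within-person SD of one void, and ρ the correlation of noise between consecutive days:

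Var = s_c² + 2 s_w² × (1 + (k − 1)ρ)/k

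The documents give none of these values. Assumed on the log scale: s_w = 0.4 and s_c = 0.5 as middle values, ranges 0.3-0.6 and 0.4-0.7, and ρ from 0 to 0.5.

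Detectable reduction at 80% power = 1 − exp(−2.8016 × √(Var × (1/61 + 1/69))), where 1/61 + 1/69 = 0.0309.

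| Voids | ρ | Variance | Cut | Detectable reduction |
|---|---|---|---|---|
| 1 | – | 0.25 + 0.32 = 0.570 | – | 31% |
| 2 | 0 | 0.25 + 0.32 × 0.50 = 0.410 | 28% | 27% |
| 2 | 0.3 | 0.25 + 0.32 × 0.65 = 0.458 | 20% | 28% |
| 2 | 0.5 | 0.25 + 0.32 × 0.75 = 0.490 | 14% | 29% |
| 3 | 0 | 0.25 + 0.32 × 0.333 = 0.357 | 37% | 25% |
| 3 | 0.3 | 0.25 + 0.32 × 0.533 = 0.421 | 26% | 27% |
| 3 | 0.5 | 0.25 + 0.32 × 0.667 = 0.463 | 19% | 28% |

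Over the whole assumed range with three voids, the cut is 18-55% if days are independent. With ρ of 0.3-0.5 it is 9% (0.67 to 0.61, at s_w 0.3, s_c 0.7, ρ 0.5) to 38% (0.88 to 0.544, at s_w 0.6, s_c 0.4, ρ 0.3).

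**3. The same question on the planning scale.** If a share f of the change variance is noise, SD = 200 × √(1 − f + f/k) for independent days. With three voids, f = 0.10 gives SD 193.2, 59 per group, and power 82.8% at 63. With f = 0.50 the figures are SD 163.3, 42 per group and 93.0%. The gain runs from small to large, and the documents do not fix f.

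**4. Baseline adjustment.** From Table 2, the baseline log SD is ln(76.2/15.1)/1.349 = 1.20, so the observed variance is 1.44. At the middle values the true between-patient variance is 1.44 − 0.16 = 1.28. If true change is unrelated to the true baseline level, residual variance after adjusting for one void = 0.25 + 0.16 + 1/(1/1.28 + 1/0.16) = 0.552, which is 3% below 0.570.

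**5. Adding the spot values.** Let v be the error variance of the mean of the two log spot values as a measure of the same baseline level. Residual variance = 0.41 + 1/(1/1.28 + 1/0.16 + 1/v).

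- v = 0.18 (assumed spot SD 0.6, two independent values): 0.489, a cut of 11%.
- v = 1.0: 0.534, a cut of 3%.

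This ignores the restriction of the spot values to 30-299. A simulation under assumed inputs gave roughly 1-12%. Even a perfectly known baseline level would leave 0.41, because the 12-month noise stays.

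**The case against.** **The count is inferred.** The article never states how many voids were taken per visit. The singular wording may name only the specimen type, and a condensed article may leave the number of containers to the full protocol. This stands as a caveat. The wording is singular throughout, and the article does give counts where more than one sample or day was meant (two spot results, three-day food diaries). A single void is the natural reading, though not a proven one.

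**The sample size is not at fault.** A reader might infer that 63 per group is too few because noise was overlooked. The documents do not support that. The figure reproduces, and its SD belongs to the change and may already contain the noise.

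**Table 2 does not measure the noise.** It is tempting to read a lower quartile of 15.1 mg/g, in patients selected on two values of 30-299, as proof of how poorly single voids agree. That comparison mixes specimen type, selection on the spot values, elapsed time and noise. It cannot identify the within-person SD of a first-morning void.

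**Consecutive mornings may share noise**, through diet, glycaemia or blood pressure. This stands. The independent-day figures are upper values.

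**Baseline adjustment might recover as much at no cost.** On the planning inputs, equal SDs of 200 and a change SD of 200 imply a correlation of 0.5. Adjustment would then give SD 200 × √0.75 = 173 and 48 per group, the same as two voids at f = 0.50. With the observed log spread and the middle values it recovers only 3%. The benefit depends on inputs that the documents do not settle.

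**The visits are over.** Abstract and Results put the last follow-up in March or April 2021. This stands, and it limits what can be changed now.

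**Conclusion.** The point holds as an inefficiency in the primary measurement. It is neither an error nor a contradiction. On the natural reading of the text, within-person noise enters the change twice. At the assumed middle values, three voids per visit would have cut the variance of the change by 37% at best, and by 19-26% with day-to-day correlation of 0.3-0.5. The smallest detectable reduction would move from 31% to 25%, or to 27-28%.

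These figures rest on an assumed within-person SD, an assumed SD of true change, an assumed correlation and the baseline group sizes; losses by 12 months would widen all of them. A claim that the trial has lost a known amount of power goes beyond the documents. The part still open to correction is the analysis, where the extra gain from the spot values is modest.

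**What to change.** **Where a visit is still open, or in a successor trial:** in Table 1, specify first-morning voids on 2-3 consecutive days at registration, 12 and 18 months, and define the visit value as their geometric mean. State the number of voids in Data Collection. The cost is one or two more home-collected containers and assays per patient per visit: for 130 patients, 260-520 extra assays over registration and 12 months (130 × 2 visits × 1 or 2), or 390-780 with 18 months included. No added visit is needed. The documents give no price, and they show mailed home voids only as a pandemic fallback.

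**For this trial:** in Statistical Analysis, specify before the results are seen that log albuminuria at 12 months is compared between groups with adjustment for the log registration void. Add the mean of the two log pre-enrolment spot values as a second baseline covariate where they are recorded; Data Collection does not list them among the registration data, so their availability must be checked. Where only one void exists, keep it as the visit value. The cost is analysis wording and retrieval of the spot values. The noise in the 12-month void remains.

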### COVID-19 Related Adjustments

Due to the COVID-19 pandemic, we made some adjustments to ensure complete data collection if participants canceled their hospital visits to avoid infection risk. The Research Ethics Committee of The University of Tokyo Graduate School of Medicine and its affiliated institutions formally approved adjustments to the trial protocol. First, we adopted a self-administered blood collection kit to measure blood glucose, HbA_1c_, eGFR, HDL-C, LDL-C, and TG levels when participants canceled in-person hospital visits. Albuminuria levels were also measured using the first-morning void mailed with the self-collected blood sample. We can conduct a blood examination by collecting 65 µl of blood from a fingertip with the self-administered blood collection kit, Ouchide-doc (Halmek Ventures, Inc). It is reported that the assay results with this blood collection method are quite comparable to the conventional methods used in hospitals [33]. Second, to minimize the face-to-face contact for data collection, we sent questionnaires to participants' homes in advance of their hospital visits.

### Ethics and Dissemination

The study is being carried out in compliance with the Declaration of Helsinki. This protocol and informed consent forms were approved by the Research Ethics Committee of The University of Tokyo Graduate School of Medicine and affiliated institutions. This study was registered in the University Hospital Medical Information Network Clinical Trials Registry (UMIN000033261) [34].

All participants are included after providing their signed and informed consent to participate in the trial. The participants are also informed of their right to withdraw from the study at any time. After the study concludes, data will be accessible by study groups for analysis and dissemination. All results of any analyses will be presented at major national and international scientific conferences and submitted for peer-reviewed journals of international repute and visibility.

### Statistical Analysis

Data regarding patients’ characteristics are presented as mean (SD) or median (IQR). We will compare changes in albuminuria levels, physical parameters, blood tests, and nutritional intake between the intervention and control groups. These will be analyzed using the 2-tailed *t* test or Mann-Whitney U test, as appropriate. Changes in J-SDSCA, MMAS-8, and JP-ADDQoL scores will also be analyzed using the Mann-Whitney U test. We will compare the proportion of hypoglycemia during the study in the intervention group to the proportion in the control group using Fisher's exact test. *P* values <.05 will be considered statistically significant. Statistical analyses will be performed using SAS (version 9.4; SAS Institute Inc).

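### The primary comparison is an unadjusted change in albuminuria by t test or Mann-Whitney test; a baseline-adjusted analysis of log UACR would be more precise with data already collected

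*Protocol article*

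**What the plan says.** The Statistical Analysis section covers the primary outcome and several secondary ones in one sentence: "We will compare changes in albuminuria levels, physical parameters, blood tests, and nutritional intake between the intervention and control groups". The method is a 2-tailed t "test or Mann-Whitney U test, as appropriate". No transformation, covariate or selection rule is given.

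The same article supplies four relevant facts:

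- **Allocation** (Participants): "The participants were randomized into either the intervention or control group in a one-to-one fashion based on albuminuria levels, gender, and age".
- **Baseline** (Data Collection and Table 1): first-morning-void albuminuria is measured at registration and at 12 months.
- **Sizing** (Sample Size): the baseline assumption is that "baseline first-morning-void albuminuria level would be 200 plus or minus 200 mg/g creatinine". The difference in change between the intervention group and "the control group at 12 months would be 100 plus or minus 200 mg/g creatinine". The stated aim is "to achieve a 2-sided significance level of .05 and a statistical power of 80"%. All of this is in untransformed mg/g.
- **Observed baseline** (Table 2): median UACR is 36.4 mg/gCr with quartiles 15.1 and 76.2. By arm, the medians are 32.3 (control) and 41.0 (intervention), P=.49.

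**The concern.** On the mg/g scale, the change in a skewed ratio is dominated by the few patients with high values. A t test on that change is noisy. A rank test copes better but still uses a change whose spread depends on the starting level. Neither uses the correlation between baseline and 12-month values beyond simple subtraction, and neither uses the factors on which allocation was based.

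At stake is the chance of detecting a real effect on the only primary outcome. A second question is whether two named tests without a selection rule put the type I error at risk.

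**Working it through.** **1. The plan's own figure.** From Sample Size: difference 100, SD 200, two-sided 0.05, power 80%.

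n per group = 2 × (1.960 + 0.842)² × (200/100)² = 62.8, so 63.

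The stated 63 is reproduced, and it is an unadjusted calculation in mg/g. That is the basis for reading the planned change as raw mg/g.

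**2. Skew.** From Table 2, the upper quartile lies 76.2 − 36.4 = 39.8 above the median and the lower 36.4 − 15.1 = 21.3 below it. On the log scale the distances are ln(76.2/36.4) = 0.74 and ln(36.4/15.1) = 0.88, which is much closer to symmetric. The log SD is ln(76.2/15.1)/1.349 = 1.20.

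**3. Value of adjustment on one scale.** With baseline-to-12-month correlation r and equal variances, the variance is proportional to 2(1 − r) for a change score and to 1 − r² for ANCOVA. The ratio is (1 + r)/2. ANCOVA therefore needs 75% of the patients at r = 0.5, 85% at 0.7 and 90% at 0.8.

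**4. Simulated power.**

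- From the article: 61 control and 69 intervention patients (baseline counts), median 36.4, log SD 1.20.
- Assumed, not in the article: lognormal UACR, log-scale r of 0.5 to 0.8, and a treatment effect that multiplies UACR by 0.6 or 0.7.
- The runs were repeated with baseline cut off at 299 mg/g, the upper limit for spot urine in the inclusion criteria.
- There were 4,000 simulated trials per row without the cut and 3,000 with it. The ANCOVA adjusts for log baseline only.

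| Reduction | r | Baseline cut | t, raw change | Mann-Whitney, raw change | t, log change | ANCOVA, log |
|---|---|---|---|---|---|---|
| 40% | 0.5 | none | 27% | 49% | 67% | 79% |
| 40% | 0.7 | none | 39% | 69% | 87% | 92% |
| 40% | 0.8 | none | 50% | 85% | 97% | 98% |
| 40% | 0.5 | 299 | 46% | 55% | 71% | 80% |
| 40% | 0.7 | 299 | 59% | 73% | 88% | 92% |
| 40% | 0.8 | 299 | 73% | 87% | 97% | 98% |
| 30% | 0.5 | none | 17% | 28% | 39% | 49% |
| 30% | 0.7 | none | 22% | 42% | 58% | 65% |
| 30% | 0.8 | none | 30% | 59% | 76% | 80% |
| 30% | 0.5 | 299 | 25% | 30% | 40% | 48% |
| 30% | 0.7 | 299 | 34% | 46% | 59% | 64% |
| 30% | 0.8 | 299 | 48% | 61% | 77% | 80% |

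Repeat runs agreed within about three points. Differences between columns, over all rows:

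- Log ANCOVA against raw Mann-Whitney: 11 to 30 points.
- Log ANCOVA against the raw t test: 23 to 53 points. The log scale alone gives 15 to 48 of these.
- Log ANCOVA against a t test on log change: 1 to 12 points, which is the part due to baseline adjustment.

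**5. Type I error.** With no effect, each test alone rejects in about 5% of trials or slightly fewer. Choosing by a Shapiro-Wilk test on the changes gives 4.8-5.3% and selects Mann-Whitney in essentially every trial. Taking whichever test has the smaller p value gives about 7-8%. When there is an effect, the two tests disagree on significance in about 17-37% of trials.

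**6. Baseline difference.** Treat the arm medians as geometric means. The part of an unadjusted log change due to regression to the mean is then 1 − (32.3/41.0)^(1 − r): 11% at r = 0.5 and 5% at r = 0.8. It runs in the direction of an apparent reduction in the intervention arm.

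**The case against.** The strongest reply is that both named tests are valid, and that the wording ordinarily means choosing by distribution. That stands. The authors already summarise UACR by median and quartiles, so Mann-Whitney is the likely test and the fair comparator. The low t-test figures describe a test that would rarely be used, and they depend heavily on whether the baseline tail is cut at 299 mg/g.

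A reader might infer more than the article supports:

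- **That the open choice inflates type I error.** It does so only if the choice follows the results, and nothing in the article says that it will.
- **That the baseline medians reveal a bias.** The difference is compatible with chance (P=.49), and a change score already subtracts baseline. Only the regression-to-the-mean part remains.
- **That ignoring the allocation factors makes the test invalid.** It tends to make the standard error conservative. Sex and age were not simulated, so no gain from them is shown.
- **That Mann-Whitney cannot give an effect in mg/g.** The Hodges-Lehmann shift does.

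Two further limits stand. The raw scale is inferred; if changes were analysed as logs, a t test would lose only 1 to 12 points. A multiplicative effect also favours a log analysis by construction.

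It may also be said that an article leaves such detail to an analysis plan. But this one does state its primary method, and the point concerns that stated method.

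**Conclusion.** The concern holds as one of efficiency. The stated analysis is valid at 5% but gives up precision that the collected data would supply. Against the more likely of the two tests, Mann-Whitney on raw change, the loss is about 11 to 30 points of power for a 30-40% reduction. That rests on the assumed correlation of 0.5 to 0.8, the multiplicative effect, the inferred mg/g scale and baseline counts; 12-month numbers may be lower. Most of the shortfall of the raw t test comes from the scale rather than from the missing covariates. Adjustment adds a smaller gain and removes the regression-to-the-mean part of the chance baseline difference. Because the two tests can disagree, one should be named, although the article gives no sign that the choice would be made by result.

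**What to change.** Before the analysis, name one primary analysis: ANCOVA of log 12-month first-morning-void UACR on arm, log baseline UACR, sex and age. Log baseline UACR stands for the albuminuria factor in the allocation. Report the adjusted geometric mean ratio with its 95% CI, and keep Mann-Whitney on the change as a sensitivity analysis. If an analysis plan already fixes a single method, bring the article's sentence into line with it.

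The cost is a change of wording; every covariate is already collected. The one drawback is that the effect becomes a ratio rather than the mg/g difference on which the trial was sized. A difference in mg/g can be given alongside as a descriptive figure. Since follow-up is reported as complete, the choice should be recorded and dated before outcomes are compared by arm.

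### Blood tests, BMI and blood pressure are measured at several visits, but the stated two-sample test on change ignores the other visits and does not adjust for baseline

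*Protocol article*

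**What the plan says.** Statistical Analysis in the protocol article states the comparison, "We will compare changes in albuminuria levels, physical parameters, blood tests, and nutritional intake between the intervention and control groups", and the method: "These will be analyzed using the 2-tailed *t* test or Mann-Whitney U test, as appropriate". It names no time point for the secondary changes, no covariate and no rule for missing values.

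Table 1 under Data Collection marks blood tests (HbA1c, fasting glucose, eGFR, lipids) at registration and at 2, 6, 12 and 18 months. Physical parameters (BMI and blood pressure) are marked at registration and at 6, 12 and 18 months.

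Three further statements bear on missing values:

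- Data Collection: "Even if the interventional treatment was discontinued, we collected as much information as possible with the consent of participants".
- COVID-19 Related Adjustments: "First, we adopted a self-administered blood collection kit to measure blood glucose, HbA_1c_, eGFR, HDL-C, LDL-C, and TG levels when participants canceled in-person hospital visits". Urine could be mailed with the blood sample. No substitute is named for BMI or blood pressure.
- Participants: "If 3 weeks passed without a patient inputting any data, we defined the patient as a dropout".

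**The concern.** A t test or Mann-Whitney test on change needs two values per patient: baseline and the visit in question. It has three limits with this schedule.

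1. A patient with HbA1c at 2 and 6 months but not at 12 adds nothing to the 12-month comparison unless the missing value is imputed. Separate tests at every visit have the same limit, because each uses only the patients seen at that visit.
2. Subtracting baseline is not adjusting for it. When the correlation between visits is moderate, a change score is noisier than a baseline-adjusted follow-up value.
3. If loss depends on earlier response differently in the two arms, the patients who remain are no longer a fair comparison.

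The third limit is plausible here. After randomization only the intervention arm uses the app, and the run-in in which every patient used it lasted 2 weeks, less than the 3 weeks without input that define a dropout. That rule can therefore act only on app users.

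What is at stake is the trial's account of how the app works. The Abstract and Discussion attribute the expected fall in albuminuria to better glycemic control, so a distorted or imprecise HbA1c comparison weakens that account.

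**Working it through.** **The plan's own figure.** The only sample-size figure is for the primary outcome: 2 × (1.96 + 0.84)² × 200² / 100² = 62.7 (62.8 with unrounded quantiles), which rounds up to 63 per group as stated. Raising 63 to 80 implies a loss of 1 − 63/80 = 21%. That allowance includes ineligibility, so it is not a month-12 missing rate. No figure is given for the secondary outcomes, and what follows is an illustration for HbA1c.

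**Inputs from the article.** There are 61 control and 69 intervention patients (Table 2). The HbA1c quartiles are 7.0 and 8.0, so the SD is about (8.0 − 7.0)/1.349 = 0.74 if roughly normal. The effect is 0.4 points, the fall the Discussion reports for the predecessor system.

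**Assumptions.** Month-12 missingness is 10% or 20%, and correlation between visits is 0.4 to 0.7. The documents give neither.

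**Precision from baseline alone.** With equal variances and correlation r, a change score has variance 2σ²(1 − r) and a baseline-adjusted value has σ²(1 − r²). The ratio of standard errors is √((1 + r)/2).

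- r = 0.4: √0.70 = 0.837, about 16% smaller.
- r = 0.6: √0.80 = 0.894, about 11% smaller.

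**Precision of the full repeated-measures model.** Simulated with visits at 0, 2, 6, 12 and 18 months, long-run correlation r and random missingness (1,500 trials per setting):

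| r | missing | SE, change test | SE, model | reduction |
|---|---|---|---|---|
| 0.4 | 10% | 0.145 | 0.120 | 17% |
| 0.4 | 20% | 0.154 | 0.126 | 18% |
| 0.6 | 10% | 0.116 | 0.104 | 10% |
| 0.6 | 20% | 0.126 | 0.110 | 13% |

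Set against 16% and 11%, nearly all of the gain comes from baseline. A second simulation isolates the earlier visits (visits at 0, 2, 6 and 12 months, equal correlation 0.5 or 0.7, 4,000 runs per setting). It compares completers' month-12 change with an estimate that uses months 2 and 6 to recover missing month-12 values. With the same missingness mechanism in both arms, the standard error fell by only about 1-4%, for example from 0.147 to 0.141 (4%) and from 0.112 to 0.110 (2%).

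**Bias.**

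- *Same mechanism in both arms* (random, or driven by rise in HbA1c to month 6): in the second simulation, bias was within 0.003 of zero for both methods.
- *Loss in the intervention arm driven by poor change from 0 to 6 months:* the completers' test overstates the benefit. In the first simulation (odds ratio 2.7 per 0.74-point change) the overstatement was 0.040, 0.082, 0.030 and 0.057 in the order of the table. In the second (logit slope 1.5 per SD of change, control loss random) it was 0.046 and 0.083 at r = 0.5, and 0.034 and 0.062 at r = 0.7, for 10% and 20% missing. Relative to 0.4, the extremes are 0.030/0.4 = 8% and 0.083/0.4 = 21%. Estimates using the earlier visits stayed within 0.003 of zero.
- *Loss driven only by the month-6 level:* the completers' test was essentially unbiased in the first simulation.

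**The case against.** The article says less than a critic may read into it. A reader might infer that patients without a month-12 value are dropped and that the 2- and 6-month data go unused. Neither is stated. No missing-data rule is given, no secondary time point is fixed, and tests at every visit would fit the wording. A missing-data method may sit in a document that is not shown, and its absence from a journal article is not a fault. This stands, and the point is limited to the test that is named.

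A reader might also take the COVID-19 section as proof that data were lost. It describes what was arranged "we made some adjustments to ensure complete data collection if participants canceled their hospital visits to avoid infection risk", and the home kit covers the very blood tests at issue. Collection after discontinuation helps too. A cancelled visit, or dropout under the no-input rule, need not mean a missing HbA1c. This also stands for blood tests. It does not answer the point for BMI and blood pressure.

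The bias needs a particular mechanism at assumed rates, and even then 0.03 to 0.08 is smaller than the standard errors of the comparison. Most of the precision gain is baseline adjustment, not a reward for extra visits. Both are correct and set the size of the point.

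Finally, a two-sample test on change is a valid randomized comparison when data are complete or missing completely at random. That is true, but it remains less precise than a baseline-adjusted analysis and has no protection when loss is response-related.

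**Conclusion.** The point holds as a criticism of a stated method. For outcomes measured at three or four follow-up visits, a two-sample test on change at any one visit neither adjusts for baseline nor uses the other visits, and without imputation it leaves out patients missing that visit.

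The surer gain is precision: a standard error about 10-18% smaller, assuming visit correlation of 0.4 to 0.6. Bias is only a possibility. It is near zero if missingness works the same way in both arms, and 0.03 to 0.08 HbA1c points if 10-20% are missing and loss in the intervention arm follows poor earlier response. The no-input dropout rule makes arm-dependent loss plausible but does not show that it occurred.

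A reader might conclude that the secondary results are biased, or that the primary result is affected. The documents support neither. They give no month-12 missing rate, and first-morning-void albuminuria has no measurement between registration and month 12 (month 6 is a spot urine). The change is worth making, for secondary outcomes only.

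**What to change.** For HbA1c, eGFR, lipids, glucose, BMI and blood pressure, make the main secondary analysis a mixed model for repeated measures, one per outcome. Include arm, visit, arm-by-visit and baseline, use the log scale for skewed tests, and include all randomized patients with any follow-up value. Report the 12-month arm difference with its 95% CI as the main secondary estimate and the 18-month difference as persistence. Keep the t test or Mann-Whitney test as a sensitivity analysis. Report the number missing by arm and visit, so that readers can judge whether arm-dependent loss arose.

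The cost is a change of analysis wording and a few hours of SAS programming on data already collected. The downside is reliance on a missing-at-random assumption, which should be stated. If the arms have already been compared, label the model as added afterwards.
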